## Abstract

**Background:**

Hypertensive disorders of pregnancy (HDP) pose significant risks to both maternal and fetal health, contributing to global morbidity and mortality. Management of HDP is complex, particularly because of concerns regarding potential negative effects on utero-placental circulation and limited therapeutic options due to fetal safety. Our study investigates whether blood pressure monitoring through a mobile health (mHealth) application can aid in addressing the challenges of blood pressure management in pregnant individuals with HDP. Additionally, we aim to assess whether this intervention can improve short-term maternal and fetal outcomes and potentially mitigate long-term cardiovascular consequences.

**Methods:**

This prospective, randomized, single-center trial will include 580 pregnant participants who meet the HDP criteria or who have a heightened risk of pregnancy-related hypertension due to factors such as multiple pregnancies, obesity, diabetes, or a history of HDP in prior pregnancies leading to preterm birth. Participants will be randomized to either the mHealth intervention group or the standard care group. The primary endpoint is the difference in systolic blood pressure from enrollment to 1 month after childbirth. The secondary endpoints include various blood pressure parameters, obstetric outcomes, body mass index trajectory, step counts, mood assessment, and drug adherence.

**Conclusions:**

This study emphasizes the potential of mHealth interventions, such as the Heart4U application, to improve blood pressure management in pregnant individuals with HDP. By leveraging technology to enhance engagement, communication, and monitoring, this study aims to positively impact maternal, fetal, and postpartum outcomes associated with HDP. This innovative approach demonstrates the potential of personalized technology-driven solutions for managing complex health conditions.

**Trial registration:**

ClinicalTrials.gov NCT05995106. Registered on 16 August 2023.

**Supplementary Information:**

The online version contains supplementary material available at 10.1186/s13063-024-08200-y.

## Introduction

### Background and rationale {6a}

Hypertensive disorders of pregnancy (HDP), encompassing chronic hypertension, gestational hypertension, preeclampsia, and preeclampsia superimposed on chronic hypertension, remains a significant contributor to maternal and fetal morbidity and mortality worldwide [1, 2]. Moreover, a history of HDP heightens the risk for future cardiovascular events [3, 4]. With the recent surge in the prevalence of advanced maternal age, there has been a simultaneous increase in the incidence of HDP, particularly in older expectant mothers [5, 6].

Effectively managing HDP not only addresses immediate maternal and fetal health but also has the potential to impact long-term adverse cardiovascular outcomes for the mother. However, the availability of pharmaceutical agents for controlling HDP is limited due to concerns regarding fetal safety [7, 8]. Consequently, active monitoring of both blood pressure and obstetric parameters plays a critical role in achieving optimal control and mitigating potential complications associated with HDP [9].

The benefits of mobile health (mHealth) for blood pressure management are well-established [10]. Our team has prior experience in developing and implementing the Heart4U application (Fig. 1), a hospital-integrated cardiovascular disease management application [11]. This application has been successfully applied in cardiovascular patients, demonstrating that its active utilization can effectively lower blood pressure and mitigate the risk of cardiovascular disease.

**Fig. 1 Fig1:**
[figure not shown]
Heart4U Application. A view of the Heart4U application from the **A** patient’s perspective in the smartphone application and **B** doctor’s perspective on an electronic medical record (EMR) system

Given that expectant mothers nowadays are typically familiar with smartphone applications [12], we aspire to actively involve this demographic in proactive blood pressure management. Through the adoption of the Heart4U application, our research endeavors to provide active support for enhanced blood pressure control in the context of HDP, thus improving the outcomes associated with this condition. This study, aligning the convenience of technology with the challenge of managing HDP, aims to positively affect the health and well-being of mothers and infants.

### Objectives {7}

#### Research hypothesis

Through proactive blood pressure monitoring, better compliance with blood pressure measurement will result in improved blood pressure control. Additionally, healthcare providers will have the capability to promptly access and review this data within the electronic medical records system during clinical consultation, facilitating more effective patient care.

#### Primary objective

The primary objective of this study is to evaluate the difference in systolic blood pressure (SBP) measured between the point of enrollment and the conclusion of the study, which is set at 1 month ± 1 week after childbirth.

#### Secondary objectives

To track the trajectory of blood pressure (systolic, diastolic, and mean) within the study duration.To assess obstetric outcomes, including:Utilization of antihypertensive medication.Progression to severe preeclampsia or eclampsia.Incidence of pulmonary edema.Occurrence of fetal growth restriction.Presence of oligohydramnios.Occurrence of preterm placental abruption.Rate of preterm delivery (between 20 and 37 weeks).Incidence of miscarriage (before 20 weeks).Frequency of fetal demise.Evaluation of newborn weight.Assessment of low birth weight.Incidence of postpartum hemorrhage (including transfusion).

### Trial design {8}

This prospective study is a randomized, single-center, open-label pragmatic trial, employing a parallel, 1:1 ratio allocation group, and superiority framework (Fig. 2). The study aims to enroll 580 pregnant individuals with HDP and comprised two intervention groups. The control group will receive standard care, while the comparison group will receive standard care along with the use of Heart4U application for proactive blood pressure measurement. Observations will be conducted in accordance with the antenatal examination schedule. Additionally, clinical follow-up will be conducted for 1 month ± 1 week after childbirth.

**Fig. 2 Fig2:**
[figure not shown]
Study flowchart. A flowchart of the study protocol. HDP, hypertensive disorders of pregnancy; mHealth, mobile health

## Methods: participants, interventions, and outcomes

### Study setting {9}

Our study takes place at Seoul National University Bundang Hospital, a tertiary medical institution situated in the suburban area of Gyeonggi Province, South Korea. The hospital boasts a substantial capacity of 1400 beds, catering to a diverse range of medical needs. Within out institution, the obstetrics and gynecology department operates a specialized high-risk maternal and neonates in Gyeonggi Province since 2016. Annually, our center facilitates over 1200 births, with approximately 70% of patients classified as high-risk pregnancies. This significant proportion underscores our advanced capabilities in managing complex maternal health issues. Notably, more than 20% of these high-risk cases involve pregnancies complicated by hypertensive disorders, highlighting the relevance and significance of our study. One distinguishing feature of our center is the well-established collaborative system between the obstetrics and cardiology departments, particularly in the management of pregnant women with high blood pressure.

### Eligibility criteria {10}

#### Inclusion criteria

Our prospective study plans to enroll 580 pregnant individuals who meet one of the following criteria for HDP [13].Chronic hypertension, defined as diagnosed hypertension within the first 20 weeks of gestation (elevated office or clinic blood pressure ≥ 140/90 mmHg) or ongoing antihypertensive medication usageGestational hypertension which involves pregnant individuals newly diagnosed with hypertension after the 20 weeks of gestation (elevated office or clinic blood pressure ≥ 140/90 mmHg) or those receiving antihypertensive treatment.Preeclampsia, characterized by new-onset hypertension after 20 weeks of gestation (elevated office or clinic blood pressure ≥ 140/90 mmHg) along with concurrent indicators such as proteinuria, thrombocytopenia, abnormal renal function, elevated liver enzymes, neurological symptoms, and pulmonary edema.Superimposed preeclampsia in pregnant individuals diagnosed with hypertension within 20 weeks of gestation or those on antihypertensive medication who experience symptoms or signs associated with this condition.Individuals with a heightened risk of pregnancy-related hypertension due to factors such as multiple pregnancies, obesity, diabetes, or a history of hypertension-related disorders in prior pregnancies leading to preterm birth.Prospective participants should be 18 years or older, possess a smartphone, be capable of using applications, and be proficient in the Korean language.

#### Exclusion criteria

Several exclusion criteria have been established to ensure the safety and feasibility of this study.Pregnant individuals requiring immediate delivery due to severe preeclampsia or eclampsia are excluded.Individuals displaying evidence of conditions such as delirium, confusion, or other altered states of consciousness, which can significantly impact a participant’s ability to provide informed consent, adhere to the study protocol, and accurately report outcomes.Patients for whom the research process would be deemed unmanageable by the investigators.Individuals with significantly limited mechanical compatibility that would impede data collection are excluded from the study to ensure that participants possess the necessary capability to independently use the application.

### Who will obtain informed consent? {26a}

Our trained research nurse and investigators provide oral and written information to the pregnant individuals with HDP. The patients can pose questions to the researchers and are afforded time to reflect upon the information before providing written consent. The nurse then collected written consent from the patients who are willing to participate. All sample information sheets and consent forms used are available in the Korean language (Supplementary file). No identifying images or other personal or clinical details of participants are presented here or will be presented in reports of the trial results. The participant information materials and informed consent form are available from the corresponding author upon request.

## Interventions

### Explanation for the choice of comparators {6b}

The participants follow the 2022 Korean Hypertension Treatment Guidelines [14]. These guidelines recommend ambulatory blood pressure monitoring for pregnant individuals with hypertension to avoid unnecessary medication. Pharmacological treatment is initiated for severe hypertension (≥ 160/110 mmHg), aiming to lower blood pressure below 150/100 mmHg without reducing diastolic pressure below 80 mmHg excessively. Postpartum, efforts are made to maintain blood pressure below 140/90 mmHg. The choice of medication considers prior usage, side effects, and fetal risk.

### Intervention description {11a}

All study participants receive the standard care and continue to receive the same proactive treatment. They are provided with OMRON automatic blood pressure monitors and are instructed by the research nurse to measure their blood pressure once daily in a quiet environment; after a minimum of 5 min of rest, participants will undergo three consecutive blood pressure measurements, each taken at 5-min intervals. The mean of the second and third measurements is recorded. Based on the measured blood pressure, if necessary and at the discretion of the treating physician, adjustments or new prescriptions for antihypertensive medications will be made.

In the intervention group, participants also receive education from the research nurse on installing and navigating the Heart4U application. At the registration point and every 2 weeks thereafter, the usage and input levels of all participants will be monitored. Participants who log in less than three times in a 2-week period will be contacted to address any issues they might face with application usage. Furthermore, in the group using the Heart4U application, medical professionals will review the information recorded in the app through the integrated electronic medical records during antenatal visits. Both groups undergo observations in accordance with the antenatal examination schedule, and the clinical follow-up period will be 1 month after childbirth.

### Criteria for discontinuing or modifying allocated interventions {11b}

Participants have the autonomy to discontinue their involvement in the trial at any juncture without needing to provide further explanations. In the event of participant withdrawal, missing data will be handled through inverse probability weighting and worst-case imputation schemes as part of the sensitivity analyses. Additionally, no crossover from the control arm to the intervention arm will be permitted during the follow-up period. Furthermore, even in the event of crossover from the control arm to the intervention arm, follow-up will continue as per the intention-to-treat (ITT) analysis protocol.

### Strategies to improve adherence to interventions {11c}

Adherence in this study is determined by the frequency of blood pressure measurements and the regularity of logging into the Heart4U application in the intervention group. The study team monitors adherence during clinical visits scheduled for antenatal examinations. To enhance adherence, the research nurse conducts regular assessments during clinical visits, ensuring that participants encounter no difficulties with using the blood pressure monitor and the application. Additional education is provided as needed to address any challenges and optimize participant engagement with the intervention.

### Relevant concomitant care permitted or prohibited during the trial {11d}

No relevant concomitant care is specifically permitted or prohibited. Managing blood pressure in pregnant individuals can be challenging due to the potential impact on utero-placental circulation and the risk of fetal anomalies associated with various medications. Given these considerations, there are typically no additional restrictions imposed on concomitant care in this trial to ensure that participants receive comprehensive and appropriate management for their HDP.

### Provisions for post-trial care {30}

No provisions are anticipated for post-trial care.

### Outcomes {12}

#### Primary outcome

The primary endpoint of this study is the difference in SBP measured between the point of enrollment and the conclusion of the study, which is 1 month ± 1 week after childbirth.

#### Secondary outcomes

Trajectory blood pressure: Throughout the study duration, trajectories of systolic, diastolic, and mean blood pressure will be tracked.Obstetric outcomes: This includes but is not limited to:Antihypertensive medication useProgression to severe preeclampsia or eclampsiaPulmonary edemaFetal growth restrictionOligohydramniosPreterm placental abruptionPreterm delivery (between 20 and 37 weeks)Miscarriage (before 20 weeks)Fetal demiseNewborn weightLow birth weightPostpartum hemorrhage (including transfusion)Trajectory of body mass index (BMI): analysis of BMI trajectory.Physical activity monitoring: step counts recorded through Samsung Health or iPhone-Health applications.Depressive Mood Assessment: depressive symptoms will be assessed using surveys, including the Patient Health Questionnaires-9 and Beck Depression Inventory [15, 16], administered at enrollment and at the conclusion of the study. These tools are widely recognized and validated measures for evaluating depression symptoms and severity.Drug adherence: evaluation of medication adherence through pill counts

#### Rationale for outcomes

Our research aims to provide active support for enhanced blood pressure control in the context of HDP, thereby improving outcomes associated with this condition. By aligning the convenience of technology with the challenge of managing HDP, this study endeavors to positively affect the health and well-being of both mothers and infants. Through comprehensive monitoring and assessment of various outcomes, including blood pressure trajectories, obstetric outcomes, physical activity levels, mood, and medication adherence, we seek to gain insights into the effectiveness of our intervention in mitigating the adverse effects of HDP and promoting overall maternal and fetal health.

### Participant timeline {13}

The participant timeline is shown in Fig. 3.

**Fig. 3 Fig3:**
[figure not shown]
Timeline for participants

### Sample size {14}

The determination of the sample size for this study, with an intended enrollment of 580 participants, was established using specific parameters as follows [17, 18]: the mean SBP at the point of enrollment was 146 mmHg, accompanied by a standard deviation of 13 mmHg. Subsequently, the mean SBP 1 month after childbirth was projected to be 130 mmHg, with a corresponding standard deviation of 12 mmHg. The control group displayed a delta SBP of 16 mmHg, whereas the delta SBP of the intervention group was amplified by 20% to 19.2 mmHg. The required difference between the two groups for sample size computation was 3.2. Moreover, a standard deviation of 13 mmHg was attributed to the delta SBP. These considerations are further coupled with an alpha error of 0.05 and a power of 80%. Using these variables, the calculations stipulated the necessity of 261 participants within each group, culminating in a total of 522. Considering a presumed dropout rate of 10%, the required comprehensive sample size was 580 participants.

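### The 80% power is not supported for the population defined as eligible: the 3.2 mmHg effect is scaled to a 16 mmHg fall from 146 mmHg, with no allowance for women admitted on risk factors alone

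*Protocol article*

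**What the plan says.** Protocol article, Sample size {14}: "the mean SBP at the point of enrollment was 146" mmHg, with SD 13 mmHg, and "the mean SBP 1 month after childbirth was projected to be 130 mmHg". From these, "The control group displayed a delta SBP of 16 mmHg", and "the delta SBP of the intervention group was amplified by 20% to 19.2 mmHg". The difference to detect is therefore 3.2 mmHg, with SD 13 mmHg for the change, alpha 0.05 and power 80%. This gives 261 per group, 522 evaluable and 580 after 10% dropout.

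Inclusion criteria {10}: one of the listed routes into the trial is "Individuals with a heightened risk of pregnancy-related hypertension due to factors such as multiple pregnancies, obesity, diabetes" or an earlier hypertensive pregnancy that ended preterm. No blood pressure requirement is attached to this route and no limit is set on its share. The Methods paragraph of the abstract likewise offers it as an alternative to meeting the HDP criteria.

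Trial design {8}, by contrast: "The study aims to enroll 580 pregnant individuals with HDP". Recruitment {15} also describes the target as women diagnosed with HDP.

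Study setting {9} reports over 1200 births a year, about 70% of them high-risk, and adds that "more than 20% of these high-risk cases involve pregnancies complicated by hypertensive disorders". Trial status gives recruitment from September 2023 to August 2026.

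**The concern.** The effect is not an independent absolute target. It is a fixed percentage of the fall expected in controls. A woman enrolled on obesity, diabetes or a twin pregnancy may have normal pressure at enrolment and little of a 16 mmHg fall to make. Under the plan's own 20% rule she then contributes a smaller effect. Pooling women whose expected falls differ also widens the SD of the unadjusted change, and the statistical methods section names only a two-sample t-test or Mann–Whitney test for it. Both mechanisms lower power.

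The sample size section does not mention this group, and the document describes the enrolled population in two incompatible ways. The stated power is what a reader would use to interpret a null primary result. If the cohort is mixed, such a result could partly reflect dilution, and nothing in the plan would tell the reader how much.

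**Working it through.** **1. The plan's own figure.** Difference 3.2, SD 13, two-sided 0.05 (statistical methods section), 1:1 allocation, power 80%. The t-based calculation gives 260.04, rounded up to 261 per arm. Then 2 × 261 = 522 and 522 / 0.9 = 580. Power of the t-test at 261 per arm is 80.1%. The plan's arithmetic is right.

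**2. Allowing for at-risk women.** Let f be the share enrolled on risk factors only, b their mean fall in the control arm and e their treatment effect. None of these is in the document, so all three are assumptions. Women with HDP keep the planned values (fall 16, effect 3.2), and the within-group SD stays at 13.

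- Average effect: (1 − f) × 3.2 + f × e
- SD of the change: √[13² + f(1 − f)(16 − b)²]
- Power: two-sided two-sample t-test at 261 per arm

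Example with f = 0.20, b = 8 and e = 0.20 × 8 = 1.6: effect = 0.8 × 3.2 + 0.2 × 1.6 = 2.88; SD = √(169 + 0.16 × 64) = 13.39; power 69%.

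| Assumption for at-risk women | f = 10% | f = 20% | f = 30% |
|---|---|---|---|
| Fall 8, gain 20% of it (1.6) | effect 3.04, SD 13.22, power 75% | 2.88, 13.39, 69% | 2.72, 13.51, 63% |
| No fall, no benefit | 2.88, 13.86, 66% | 2.56, 14.49, 52% | 2.24, 14.93, 40% |
| Fall 8, full 3.2 gain | 3.20, 13.22, 79% | 3.20, 13.39, 78% | 3.20, 13.51, 77% |

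**3. What adjustment for HDP status recovers.** It removes the f(1 − f)(16 − b)² term, so the SD returns to 13. Power becomes 76%, 71% and 66% in the first row and 71%, 61% and 50% in the second. The diluted effect remains. Any further gain from adjusting for baseline systolic pressure is not counted here.

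**4. Is a non-trivial share plausible?** From Study setting: 1200 × 0.70 × 0.20 = 168 HDP pregnancies a year, and 168 × 3 = 504 over the 36-month window, against a target of 580. Two of the three inputs are worded as lower limits. With 23% instead of 20%, supply is 1200 × 0.70 × 0.23 × 3 = 580. With 25% it is 630; at an assumed 70% consent that yields 441, leaving (580 − 441) / 580 = 24% to come from elsewhere. With 30% it is 756; at 70% consent that yields 529, leaving 9%. The consent rate is an assumption.

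**The case against.** The strongest reply is that the loss is conditional. If the trial design and recruitment sections govern, the cohort is HDP-only and 80% stands. It also stands if 3.2 mmHg and SD 13 hold in the mixed cohort. The cited sources for 146 and 130 mmHg are not shown, so their composition cannot be checked. A normal distribution with mean 146 and SD 13 already puts about 32% below 140 mmHg, so the assumed cohort is not uniformly above the threshold. All of this stands, and it limits what can be claimed.

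A reader might infer more than the document supports in four ways:

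- **That the design does not have 80% power.** This cannot be said as fact, because neither the at-risk share nor those women's change in pressure is given.
- **That at least 13% of the 580 must be at risk**, from (580 − 504) / 580. The figures behind 504 are mostly lower limits, so 504 is roughly a floor on supply, and 13% is not a minimum. A shortfall could also appear as slow or incomplete recruitment.
- **That women with treated chronic hypertension are a further mismatch.** The sample size section does not exclude treated women from its source values.
- **That a null result would be uninterpretable.** The confidence interval would still describe the effect in the population enrolled.

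What the reply does not remove is that the 80% is stated without condition while the document disagrees with itself about who is enrolled.

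**Conclusion.** The concern holds as a mismatch between the assumptions and the eligibility criteria; it is not an arithmetic error. The 80% power is not supported for the population that the abstract and inclusion criteria define.

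If at-risk women make up 10% to 30% of the sample, power runs from about 75% down to 63% when they fall 8 mmHg and gain in proportion. It runs from about 66% down to 40% when they neither fall nor benefit. It stays at 77% to 79% if they fall 8 mmHg and gain the full 3.2 mmHg. These figures rest on the assumed share, fall and effect, on a within-group SD of 13, and on the planned unadjusted t-test. The site's figures make a non-trivial at-risk share plausible when consent is below 100%, but they do not establish a minimum.

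**What to change.** Keep 580 and make four changes.

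1. Reconcile the abstract, trial design, inclusion criteria, sample size and recruitment sections on whether women with risk factors only are part of the trial population.
2. If they are, restate the sample size section with power, or the detectable difference, over a stated range of at-risk share, giving the assumed fall and SD. Alternatively, show that 146, 130 and SD 13 describe the mixed cohort.
3. Record diagnosed HDP versus at-risk status at baseline and adjust the primary analysis for it together with baseline systolic pressure. This removes the between-group part of the SD.
4. Prespecify the treatment effect in women with diagnosed HDP as a supportive estimate.

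Leave the stratification of the randomisation as it is. Recruitment was due to open in September 2023, and changing a running allocation system is not a cheap edit; covariate adjustment does not need it.

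The cost is a less favourable stated power, some protocol wording, one baseline field if it is not already collected, and a little more analysis work. No extra participants are needed.
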